## Abstract

**Objective:**

HAPpEN aims to implement and evaluate a holistic general practitioner-centered, interdisciplinary obesity management strategy in rural Germany, focusing on feasibility, health outcomes, and economic benefits.

**Methods:**

HAPpEN is a 12-month, pragmatic single-arm, multicenter trial, informed by a formative survey, and initiated in April 2023 with 98 obese participants (body mass index, BMI ≥ 30 kg/m^2^) in Kulmbach, Germany. The program integrates nutritional counseling, physical activity, and behavior change techniques, including smartphone-based self-monitoring. Monthly consultations help set personalized goals using a multi-stage grading scale. Primary outcomes include BMI, body weight, waist circumference, heart rate, blood pressure and parameters, while secondary outcomes assess quality of life, wellbeing, health literacy, social interaction, and digital therapy support.

**Results:**

The baseline cohort (mean age: 46.9 ± 11.8 years, 74.1 % female) exhibited high obesity rates (mean BMI: 40.1 ± 6.1 kg/m^2^), with 48.5 % classified as grade III obese. Common comorbidities were hypertension (51.8 %), dyslipidemia (30.5 %) and diabetes (21.8 %). Chronic joint paint, mainly in the knees and hips, affected up to 82.4 %. A familial aggregation of obesity, diabetes, and cardiovascular diseases was noted, alongside behavioral challenges such as lack of physical activity (81.8 %) and unhealthy eating habits (56.8 %).

**Conclusion:**

HAPpEN addresses obesity's multifactorial nature through general practitioner-led, community-based, and digital strategies to promote sustainable lifestyle changes in rural areas. The trial aims to inform primary care obesity management guidelines, focusing on improving health literacy, patient engagement, and long-term clinical benefits. German Clinical Trials Register: DRKS00033916.

## Introduction

1

Obesity is primarily associated with genetic disposition, poor diet and lack of physical activity (Mensink et al., 2013). In Germany, two-thirds of men and more than half of women are overweight (body mass index, BMI 25–29.9 kg/m^2^). Approximately a quarter of adults (23.3 % for men and 23.9 % for women) are classified as obese (BMI ≥ 30 kg/m^2^). Over the past two decades, the prevalence of obesity has significantly increased globally (Blüher, 2019). This trend not only leads to high healthcare costs but also poses significant health risks, including higher all-cause mortality (Durrer Schutz et al., 2019; NCD Risk Factor Collaboration and NCD-RisC)., 2021). Economic disparities between urban and rural areas modulate obesity prevalence (Blüher, 2019). Rural populations in the United Kingdom and Australia report lower engagement in leisure-time physical activity and fail to meet recommendations. Additionally, sedentary activities like viewing television and consumption of sugar-sweetened beverages occur more often contributing to higher obesity rates (Trivedi et al., 2015; Beverly, 2024; Borders et al., 2006). In Europe, obesity levels are elevated in the south compared to the north (Berghöfer et al., 2008), with similar trends observed in Germany, particularly in rural southwestern regions (Boehm et al., 2005). More detailed works regarding obesity and German rural environments are missing, highlighting the need for tailored guidelines and support for rural settings given limited access to health-related resources.

Effective multidisciplinary programs are essential for sustained obesity prevention and treatment involving nutrition, exercise, and behavioral changes into core medical healthcare (Durrer Schutz et al., 2019; Hauner et al., 2014; Lim et al., 2021). Due to their longstanding relationships with patients, especially in rural areas, general practitioners play a crucial role in incorporating socio-cultural aspects that allow tailored and comprehensive care (Whitlock et al., 2002; Van Dijk et al., 2006). Digitalization enhances obesity treatment additionally by enabling personalized programs and support that is time- and location-independent. In Germany, there are currently few long-term, general practitioner-centered obesity prevention and treatment programs, such as M.O.B.I.L.I.S., DocWeight, EndlichVital, Gesundheit PLUS, Bodymed and ACHT-Nachsorge (Hauner et al., 2014; König et al., 2018; Göhner et al., 2012; Berg Jr et al., 2008; Rudolph et al., 2016). These programs target individuals with a BMI ≥ 30 kg/m^2^ respectively ≥25 kg/m^2^ with increased comorbidity risk, offering nutritional, sport medicine, and behavioral components, but lacking digital therapy support. ACHT-Nachsorge includes digital tracking post-bariatric surgery. However, these programs do not fully integrate a multidisciplinary approach tailored to sociocultural contexts. HAPpEN aims to fill this gap with an interdisciplinary, evidence-based (Durrer Schutz et al., 2019; Hauner et al., 2014) holistic program focused on general practitioners and social support in a rural real-world setting. HAPpEN involves general practitioners as active therapists employing psychological interventions and providing personalized advice and education on nutrition and physical activity supplemented by a digital self-monitoring diary, fostering sustained behavior change. The primary objective is to enhance medical care for obese patients in rural settings, while the secondary objective is to evaluate the feasibility, health and economic benefits in daily life over 12 months. Here, we present formative survey data informing the HAPpEN pragmatic trial protocol, and corresponding baseline data, offering a detailed overview of our patient's sociodemographic and health-related characteristics. These data were collected through physical examinations, surveys, and questionnaires conducted in a rural setting. These data highlight the research value of such regions, capturing unique insights into patient's perceived causes of overweight and motivation for trial participation. The results aim to establish, evaluate, and optimize primary care-centered obesity management guidelines, particularly for non-urban regions.

## Material and methods

2

### Formative survey

2.1

Prior to designing HAPpEN, a survey was conducted to understand the eating and physical activity habits, food environment, health information sources, and use of digital health tools among German rural residents (König et al., 2024). The survey, administered in four family practices, collected data from 273 adults over a 10-week period from December 2022 to February 2023. The survey revealed a predominantly female population with a high prevalence of overweight and obesity among rural adults aged 40 and older. Participants reported preferences for home-cooked meals, limited local dining options, low exercise habits and high reliance on digital media, highlighting the need for (digital) accessible education and engaging, culturally relevant interventions (see Supplements, Supplementary Table 1–3). Consequently, to address these barriers and preferences, HAPpEN incorporates edutainment next to the general practitioner-centered approach to spruce up learning about nutrition and physical activity. This includes general practitioner-led teaching on nutrition and physical activity guidelines and community challenges facilitated through digital media like the HAPpEN app and website with integrated exchange forum. Additional healthy recipes, in-person-edutainment activities and physiotherapist-led exercise groups were included (see Supplementary Table 3 and section 2.4).

### Design

2.2

HAPpEN is a pragmatic single-arm trial in six rural primary care offices in Kulmbach, Germany, supported by nine physiotherapists for exercise interventions. Data are collected only from patients who provided written consent, with the option to withdraw anytime. The data collection process included physical examinations, surveys, and self-reporting questionnaires. Comparative baseline data are drawn from population-based statistics in Kulmbach. All procedures were performed in compliance with relevant laws and guidelines and have been approved by the ethical institutional committee of the University of Bayreuth (Az. O 1305/1 – GB, April 2023). The trial is registered at the German Clinical Trials Register (DRKS00033916).

### Participants

2.3

For recruitment, general practitioners informed patients during routine consultations, posters were distributed in clinics and a radio advertisement was aired shortly before the trial. Patients aged 18–65 years, meeting the following inclusion criteria were enrolled in the trial:•Confirmed diagnosis of obesity (BMI ≥ 30 kg/m^2^) at the time of recruitment•Sufficient knowledge of the German language•Ability and willingness to use a digital, app-based self-monitoring diary

Patients fulfilling any of the following criteria were excluded from the trial:•Condition of incapacity for load bearing, e.g. following a surgical procedure•Patients requiring urgent major surgical intervention•Patients with seizure disorders or epilepsy•Dementia/cognitive deficit, which contradicted with the program•Psychiatric illness contradicting the program•Participation in another study (up to one month before start timepoint)•Heart failure from New York Heart Association class III onwards•Uncontrolled arterial hypertension•Severe pulmonary comorbidity (severe asthma, chronic obstructive pulmonary disease, modified Medical Research Council dyspnea scale >2 / chronic obstructive pulmonary disease assessment test >10, pulmonary fibrosis)•Severe psychiatric eating disorders•Other severe illness that rendered physical exertion impossible

The intervention targeted an area-based sample within the district of Kulmbach, focusing on the towns of Marktleugast, Presseck, Untersteinach, Thurnau, Kasendorf and Stadtsteinach. The rural population (except Untersteinach) was defined as participants from sparsely populated rural areas, characterized by low population density, a predominantly agricultural landscape and limited infrastructure (BBSR, 2024; Küpper, 2016).

### Guideline-compliant obesity management intervention

2.4

#### Overview of intervention components

2.4.1

HAPpEN is a multi-component intervention, drawing on face-to-face and digitally delivered content and promoting social support and knowledge exchange. It involved general practitioners as the primary point of contact and guide through the intervention, as well as nutrition and behavior change experts and physiotherapists. The intervention components and related behavior change techniques (Michie et al., 2015) are listed in Table 1 and are described in more detail in the following.

**Table 1 t0005:** List of HAPpEN intervention components and implemented behavior change techniques.

HAPpEN intervention component	Brief description	Behavior Change Techniques (BCT taxonomy v1) (Michie et al., 2015)
Individual goal setting and planning	Step-wise, tailored goal setting across 17 weight management and health topics (e.g. diet, physical activity, sleep), with participants selecting two to three topics/month and choosing from five to eight goal levels, this is performed via the HAPpEN app and during monthly sessions led by general practitioners	1.1 goal-setting (behavior), 1.5 review behavior goal(s), 1.6 discrepancy between current behavior and goal, 2.2 feedback on behavior, 8.7 graded tasks
Self-Management	Using action and coping planning, participants identify practical strategies for daily implementation and potential barriers, developing individualized plans to enhance adherence and manage challenges effectively	1.2 problem-solving, 1.4 action planning
Problem Solving/ Feedback	Withing general practitioner-led monthly sessions, focus on eliciting feedback, addressing personal barriers, and fostering self-reflection to enhance intrinsic motivation and support behavior change, using motivational interviewing techniques	1.2 problem-solving, 2.1 feedback on behavior, 2.7 feedback on outcome(s) of behavior
Self-monitoring	Enabling self-monitoring of dietary and activity goals, weight progress curves and personalized training plans via HAPpEN app. Weight and BMI^1^ are also tracked at general practitioner practice every month.	2.3 self-monitoring of behavior, 2.4 self-monitoring of outcome(s) of behavior
Gamification	Challenges and learning units, provided digitally via the app and forum. These interactive tools incorporated regional settings and daily routines to engage participants in adopting a health-promoting lifestyle through playful and practical approaches	4.1 instruction on how to perform a behavior, 10.3 non-specific reward
Education	Providing evidence-based guidance on diet, physical activity and behavior change strategies in teaching session. General practitioner-led monthly sessions with integration of motivational interviewing and nutritional counseling	4.1 instruction on how to perform a behavior, 4.2 information about antecedents, 5.1 information about health consequences, 6.1 demonstration of the behavior, 8.1 behavioral practice/ rehearsal, 9.1 credible source
Social interaction	Facilitated through physiotherapists-led exercise group session, a peer exchange forum, and in-person activities (cooking and hiking events and barbecues), promoting social support and engagement in a health-oriented community	3.1 social support (unspecified), 3.2 social support (practical), 4.1 instruction on how to perform a behavior, 12.2 restructuring the social environment

^1^BMI, body mass index

#### Assessments by and consultations with the general practitioners

2.4.2

HAPpEN is set up in accordance with the 5 A model and the S3 Guideline for Obesity Prevention and Therapy (Hauner et al., 2014) (see Supplementary Table 4). In the first ASSESS step, eligible patients willing to change weight are identified. At enrollment, a comprehensive medical history is obtained, including a standardized physical examination, ergometry, lab testing, and self-report surveys to evaluate fitness, health status and body weight management. In addition, to prevent complications and sensibilize for their own health condition, patients undergo examinations by doctors after six and 12 months (see Fig. 1 and Table 2). Second, in the ADVICE step, patient-specific problems, causes, and obstacles to weight reduction are recorded for individual education. A therapy plan involving nutrition, exercise, and behavioral techniques is developed, tailored to the patient's initial weight, comorbidities, and weight loss goals. Third, in the AGREE step, individual goals are set step by step to be achieved within every four weeks and evaluated and discussed in the monthly appointments. Fourth, during the ASSIST step, obstacles to achieving agreed goals are evaluated. Finally, in the ARRANGE step, general practitioners use motivational interviewing techniques (Barrett et al., 2018) to sustain participants' motivation, assessing current resources and circumstances to support lifestyle changes beyond the trial.

**Fig. 1 f0005:**
[figure not shown]
Timeline of the 12-month pragmatic, single-arm HAPpEN trial from the patient's perspective. At the start, next to nutrition and behavioral education, a comprehensive medical history is taken including detailed anamnesis via surveys and a standardized physical examination (body height, weight respectively body mass index (BMI), waist circumference, blood pressure, heart and pulse rate, joint function, thoracic auscultation, abdominal examination, motor and sensory tests), supplemented by ergometry and lab tests to assess patients' fitness level and health status. Monthly appointments with general practitioners and group sessions with physiotherapists support patients in identifying performance goals and increasing muscle-strengthening exercises or physical activity in general. The HAPpEN app acts a stepwise digital diary, allowing for education and monthly nutrition and exercise goals to be set, aided by video-based training. Follow-up physical examinations are conducted at six and 12 months. Additionally, patients' perceptions of social group interactions, dynamics and social media usage are continuously assessed and documented through surveys and interviews.

**Table 2 t0010:** Data Collection within the 12-month pragmatic HAPpEN trial.^2^

	Enrolment	Pragmatic trial (months)										Trial End	Instrument	Statistics
Timepoint	1	2	3	4	5	6	7	8	9	10	11	12		
Social anamnesis	x												questionaire	Person‘s-chi-squared test
Body weight management	x												questionaire	
Wellbeing/quality of life/sleep	x/x/x^3^					−/(x)/x						x/x/x	questionaire	Analysis of Variances, t-test
Medical history (smoking, joint trouble)	x					x						x	questionaire	Cochran's Q test, Friedmann test
BMI^1^, weight, waist circumference, blood pressure, blood test, thorax-, abdomen-, neurological tests, ergometry	x					x						x	medical examination	Analysis of Variances
Medication	x					x						x	questionaire, medication plan	Cochran's Q test
Family history and diseases	x												questionaire	
Nutrition literacy eating/drinking behavior	x					x						x	questionaire	Cochran's Q test
Physical literacy and activity	x					x						x	questionaire	Cochran's Q test
HAPpEN-App												x	questionaire	t-test, correlation, regression
Technical affinity	x												questionaire	
Social support/social network	x					x						x	questionaire/ interviews/	
General practitioner-centered program						x						x	questionaire/ interviews	

^1^BMI, body mass index

^2^Data will be collected at indicated time points using shown measurement instruments. Statistical evaluation is performed utilizing the specified test.

^3^The consecutive Xs represent the individual assessments of wellbeing, quality of life, and sleep at the indicated time points. If three Xs are present, all three assessments were conducted at that time point; if only two Xs are present, only two assessments were performed accordingly.

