### Statistics

2.6

BMI and body weight will be compared between the patients in the trial and those receiving current obesity standard care. Furthermore, outcomes will be analyzed at baseline and after six and 12 months, using paired *t*-tests, analysis of variances, Cochran's Q or Friedman test (see Table 2). Data distribution will be analyzed using Shapiro-Wilk normality test and histograms.

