Medical history		baseline population
**Weight**		117.5 ± 22.0 kg (98)
**Height**		170.6 ± 7.5 cm (97)
**Waist circumference**		123.6 ± 15.2 cm (88)
**BMI**^**1**^ Obesity Grade I (BMI 30.0–34.9) Obesity Grade II (BMI 35.0–39.9) Obesity Grade III (BMI >40)		40.1 ± 6.1 kg/m^2^ (97) 22.7 % (22) 28.9 % (28) 48.5 % (47)
**Blood Pressure (systolic/diastolic)**		134.8/85,6 ± 13.7/9,0 mmHg (93)
**Heart Rate**		81.0 ± 12.9 beats/min (94)
**Comorbidities** Hypertension Diabetes Mellitus Reflux Dyslipidemia Uric acid metabolism disorder Myocardial infarction Vascular diseases Lung diseases Sleep apnea Hypothyroidism Kidney diseases Urinary incontinence Gallstone disease Chronic inflammatory bowel disease Fatty liver Joint diseases/rheumatism Knee osteoarthritis Hip osteoarthritis Spinal disc herniation Cervical disc herniation Thoracic disc herniation Lumbar disc herniation Degenerative spine syndrome Degenerative cervical spine disease Degenerative lumbar spine disease Shoulder syndrome Spinal canal stenosis Depression/depressive mood Other psychological conditions Anxiety disorders Burnout Cancer Breast cancer Thyroid cancer Other conditions: skin diseases (psoriasis, neurodermatitis), scoliosis, hip dysplasia, abdominal hernia, neurological disorders (multiple sclerosis, fatigue syndrome), allergies/hay fever, Factor V disorder, post-Coronavirus Disease syndrome, migraines, tinnitus, lymphatic diseases (lymphedema), fibromyalgia		51.8 % (44) 21.8 % (19) 27.1 % (23) 30.5 % (25) 10.7 % (9) 7.0 % (6) 5.8 % (5) 9.3 % (8) 9.4 % (8) 16.7 % (14) 4.6 % (4) 17.2 % (15) 13.8 % (12) 5.9 % (5) 20.5 % (17) 10.7 % (9) 25.0 % (21) 9.5 % (8) 18.6 % (16) 3.6 % (3) 1.2 % (1) 9.6 % (8) 22.1 % (19) 5.3 % (4) 5,3 % (4) 11.8 % (10) 6.0 % (5) 20.0 % (17) 11.1 % (9) 6.3 % (5) 2.5 % (2) 7.0 % (6) 5.8 % (5) 1.2 % (1) 17.2 % (15)
**Physical examination**		baseline population
**Auscultation of Thorax** Rhythmic hear rhythm Clear heart sound Additional heart sounds / others Diminished breath sounds Stridor / obstructive breath sounds		100 % (96) 96.9 % (93) Systolic (3rd intercostal room left) (1), tachycardia (1), paroxysmal atrial fibrillation (1) 1.0 % (1) 2.4 % (2) / 2.4 % (2)
**Abdominal Examination** Soft / distended abdominal wall tenderness Normal / pathological bowel sounds Regular bowel history Constipation / Diarrhea / irregular		98.9 % (94) / 1.1 % (1) 2.1 % (2) 98.9 % (94) / 1.1 % (1) 77.8 % (70) 8.9 % (8) / 10.0 % (9) / 3.3 % (3)

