**Neurological Examination** Symmetric / increased / decrease muscle tone Unremarkable strength assessment Intact / pathological sensation		96.8 % (90) / 2.2 % (2) / 1.1 % (1) 100 % (85) 81.5 % (75) / 18.5 % (17)
**Family medical history** Overweight/obesity in the family Diabetes mellitus in the family Hypertension in the family Dyslipidemia in the family Myocardial infarction/sudden cardiac death in the family Arteriosclerosis/vascular occlusion in the family Stroke in the family Kidney disease in the family Depression in the family Cancer in the family		81.2 % (69) 52.3 % (46) 76.5 % (65) 22.5 % (18) 44.2 % (38) 44.4 % (36) 29.8 % (25) 26.2 % (22) 29.3 % (24) 52.3 % (46)
**Joint complaints**		baseline population
General physical complaints		82.4 % (85)
Joint complaints in the past 12 months		83.9 % (87)
Joint complaints in the last 24 h		51.2 % (86)
Pain in the last 24 h Mild/Moderate/Severe	Shoulder	Left side: 11.2 % / 7.1 % / 0.0 % (98) Right side: 13.3 % / 5.1 % / 1.0 % (98)
	Elbow	Left side: 4.1 % / 1.0 % / 0.0 % (98) Right side: 6.1 % / 1.0 % / 1.0 % (98)
	Wrist	Left side: 6,1 % / 3,1 % / 0,0 % (98) Right side: 4.1 % / 5.1 % / 0.0 % (98)
	Finger joints	Left side: 13.3 % / 4.1 % / 0.0 % (98) Right side: 11.2 % / 4.1 % / 1.0 % (98)
	Hip	Left side: 8.2 % / 7.1 % / 3.1 % (98) Right side: 10.2 % / 4.1 % / 5.1 % (98)
	Knee	Left side: 11.2 % / 14.3 % / 1.0 % (98) Right side: 13.3 % / 14.3 % / 4.1 % (98)
	Ankle	Left side: 10.2 % / 9.2 % / 0.0 % (98) Right side: 6.1 % / 11.2 % / 0.0 % (98)
	Toe joints	Left side: 6.1 % / 4.1 % / 0.0 % (98) Right side: 6.1 % / 3.1 % / 0.0 % (98)
Signs of inflammation (top) Full mobility (bottom)	Shoulder	Left side: 1.1 % (93) / Right side: 0.0 % (93)
		Left side: 92.0 % (87) / Right side: 93.0 % (86)
	Elbow	Left side: 0.0 % (93) / Right side: 0.0 % (92)
		Left side: 98.8 % (83) / Right side: 98.8 % (83)
	Wrist	Left side: 0.0 % (94) / Right side: 0.0 % (93)
		Left side: 96.4 % (84) / Right side: 95.2 % (84)
	Hip	Left side: 1.1 % (92) / Right side: 0.0 % (92)
		Left side: 83.3 % (84) / Right side: 86.7 % (83)
	Knee joint	Left side: 3.3 % (92) / Right side: 4.3 % (93)
		Left side: 88.0 % (83) / Right side: 89.3 % (84)
	Ankle joint	Left side: 0.0 % (93) / Right side: 0.0 % (93)
		Left side: 100 % (83) / Right side: 100 % (83)
Pain (top) Movement restriction (bottom)	Cervical spine (C-spine)	13.3 % (90)
		15.9 % (88)
	Thoracic spine (T-spine)	4.4 % (90)
		11.4 % (88)
	Lumbar spine (L-spine)	29.8 % (94)
		33.7 % (89)

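### Table 2 assigns analysis of variance to categorical examination findings; for bowel history and muscle tone the result then depends on how the categories are numbered

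*Protocol article*

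**What the plan says.** Table 2 (in section 2.4.2) lists what is collected at enrolment, month 6 and month 12, with a last column naming the test. One row reads "BMI^1^, weight, waist circumference, blood pressure, blood test, thorax-, abdomen-, neurological tests, ergometry". Its only entry in that column is "Analysis of Variances". Footnote 2 makes the column binding: "Statistical evaluation is performed utilizing the specified test".

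Section 2.6 says outcomes are compared at baseline and after six and 12 months "using paired *t*-tests, analysis of variances, Cochran's Q or Friedman test (see Table 2". It names Cochran's Q, but leaves to Table 2 which measure gets which test. Table 2 gives Cochran's Q to other rows, such as medication, and not to this one.

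Table 4 shows how the findings are recorded. Abdominal items include regular bowel history and, separately, "Constipation / Diarrhea / irregular". Neurological items are "Symmetric / increased / decrease muscle tone Unremarkable strength assessment Intact / pathological sensation". The thoracic items are presence or absence of auscultation findings. All are given as counts and percentages, and none has a mean or standard deviation.

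**The concern.** Analysis of variance compares means across visits. BMI, weight and blood pressure have means. Regular, constipation, diarrhea and irregular have no order, so their mean exists only once someone has numbered them. Muscle tone has one normal state and two abnormal states in opposite directions, so a natural numbering (decreased −1, symmetric 0, increased +1) lets new findings in one direction cancel new findings in the other.

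At stake is whether the reported change in these two items means anything. Someone who follows Table 2 literally must choose codes that the article does not give, and that choice can decide whether the result reads as no change or as a highly significant one.

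**Working it through.** **Inputs.** Baseline counts from Table 4:
- bowel history: regular 70, constipation 8, diarrhea 9, irregular 3 (n = 90);
- muscle tone: symmetric 90, increased 2, decreased 1 (n = 93);
- sensation: intact 75, pathological 17 (n = 92).

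The printed percentages follow from these counts, for example 70/90 = 77.8 %, 90/93 = 96.8 % and 17/92 = 18.5 %. There are k = 3 visits. The article has no follow-up data, so every follow-up shift below is an assumption, taken as the same at months 6 and 12 unless stated. Analysis of variance is read as the one-way repeated-measures form, since the same patients are examined three times.

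**Formulas.**
- F = [SS_visit/(k − 1)] / [SS_error/((n − 1)(k − 1))].
- Cochran's Q = (k − 1)[kΣC² − (ΣC)²] / (kΣC − ΣR²), where C are the numbers with the finding at each visit and R is the number of visits at which each patient has it.

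**1. Bowel history.** Assume 6 regular and 6 diarrhea patients become constipated. The counts become 64/20/3/3, and constipation goes from 8/90 = 8.9 % to 20/90 = 22.2 %.
- Codes regular 0, constipation 1, diarrhea 2, irregular 3. Baseline mean (8 + 18 + 9)/90 = 0.389; follow-up mean (20 + 6 + 9)/90 = 0.389. SS_visit = 0, F = 0, p = 1.00.
- Codes regular 0, constipation 3, diarrhea 2, irregular 1. Baseline mean (24 + 18 + 3)/90 = 0.500; follow-up mean (60 + 6 + 3)/90 = 0.767. F = (4.267/2)/(35.733/178) = 10.63, p = 0.00004.
- Cochran's Q on constipation yes/no: C = 8, 20, 20; ΣR² = 8×9 + 12×4 = 120. Q = 2(3×864 − 48²)/(3×48 − 120) = 576/24 = 24.0, p = 0.000006.

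**2. Muscle tone.** Assume 6 symmetric patients become increased and 6 become decreased, giving 78/8/7.
- Codes decreased −1, symmetric 0, increased +1. Mean (2 − 1)/93 = 0.011 at baseline and (8 − 7)/93 = 0.011 at follow-up. F = 0, p = 1.00.
- Codes 1/2/3 in the order printed in Table 4. Means 97/93 = 1.043 and 115/93 = 1.237. F = (2.323/2)/(17.677/184) = 12.09, p = 0.00001.
- Cochran's Q on abnormal yes/no: C = 3, 15, 15; ΣR² = 3×9 + 12×4 = 75. Q = 2(3×459 − 33²)/(3×33 − 75) = 576/24 = 24.0, p = 0.000006.
- Cochran's Q on each direction separately: increased 2, 8, 8 gives Q = 2(3×132 − 18²)/(54 − 42) = 12.0; decreased 1, 7, 7 gives Q = 2(3×99 − 15²)/(45 − 33) = 12.0; p = 0.0025 for each.

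**3. Two-level items.** Sensation, assuming 17, 23 and 26 pathological of 92 at the three visits: F = 7.49, p = 0.0007, with either category coded 1. Cochran's Q = 14.0, p = 0.0009. For yes/no data the two are linked exactly by Q = n(k − 1)F/(F + n − 1); here 92×2×7.494/(7.494 + 91) = 14.0. In simulation without any true change (n = 93, 4,000 runs per setting), both tests rejected in 5.1 % of runs at 18.5 % prevalence and in 3.9 % at 1.1 % prevalence.

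**4. New against resolved findings.** If 8 intact patients become pathological and 8 pathological patients recover, the count stays at 17 of 92. Then F = 0 and Q = 0, with p = 1.00 for both.

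**The case against.** The strongest reply is that the error is narrow. Most of the findings in Table 4 (rhythm, heart and breath sounds, distension, tenderness, bowel sounds, strength, sensation) are two-level, and step 3 shows that the named test does little harm there. Only bowel history and muscle tone remain, and muscle tone has 3 abnormal findings among 93 patients. The shifts in steps 1 and 2 are built to cancel under one numbering. The article gives no codes, and Table 4 prints a separate count for each bowel category; analysed as separate yes/no indicators, the dependence on codes disappears.

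Most of this stands and sets the scope. It does not remove the point. The article nowhere says that separate indicators will be used, and Table 2 with its footnote fixes a test of means for these items. Nor is this a detail left to an unseen analysis plan, since the test is stated.

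A reader might infer more, in three ways that the documents do not support.
- **That analysis of variance hides new abnormal findings in the yes/no items.** Step 4 shows that Cochran's Q nets new against resolved findings in the same way. This is a property of any test of net change.
- **That the trial's check for complications, or its feasibility and health-benefit conclusions, would fail.** Section 2.4.2 says "to prevent complications and sensibilize for their own health condition, patients undergo examinations by doctors after six and 12 months". That describes the care of individual patients, whose doctor sees each finding whatever group test is run. Section 2.5 names none of these findings as a primary or secondary outcome; its disease-burden examples are medication, comorbidities and sleeping behavior.
- **That the Friedman test is the planned fallback after the Shapiro-Wilk check.** Section 2.6 mentions both but states no such rule.

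**Conclusion.** The test assignment in Table 2 is wrong for the thoracic, abdominal and neurological findings. It has a real consequence for two items: for bowel history and muscle tone, the same data can give p = 1.00 or p < 0.001 depending only on the numbering. These figures rest on assumed follow-up shifts and assumed codes. They show what the stated test allows and do not predict the trial's result. For the two-level items the change of test is mainly a matter of using the appropriate model. Severity is minor, because none of these findings is a named outcome and no clinical management rule is involved.

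**What to change.** Split the row in Table 2.
- Keep analysis of variance for BMI, weight, waist circumference, blood pressure, blood values and numeric ergometry results.
- For the thoracic, abdominal and neurological findings, predefine normal/abnormal indicators and analyse each with Cochran's Q over the three visits. Use separate indicators for constipation and diarrhea, and for increased and decreased muscle tone.
- Optionally, tabulate new and resolved findings from enrolment to month 6 and to month 12. No test of net change shows these.

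The cost is a change of wording in one row and a few extra tables. All the data are already collected: "Follow-up physical examinations are conducted at six and 12 months". The downside is sparse counts. Some items have one abnormal finding or none at baseline (bowel sounds 1 of 95; heart rhythm normal in 96 of 96). If no abnormal finding occurs at any visit, Cochran's Q is undefined and the count alone should be reported.
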